## Abstract

**Background:**

Migraine is a chronic neurologic disease that can severely affect the patient's quality of life. Although in recent years many randomised studies have been carried out to investigate the effectiveness of acupuncture as a treatment for migraine, it remains a controversial issue. Our aim is to determine whether acupuncture, applied under real conditions of clinical practice in the area of primary healthcare, is more effective than conventional treatment.

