**Methods/Design:**

The design consists of a pragmatic multi-centre, three-armed randomised controlled trial, complemented with an economic evaluation of the results achieved, comparing the effectiveness of verum acupuncture with sham acupuncture, and with a control group receiving normal care only.

Patients eligible for inclusion will be those presenting in general practice with migraine and for whom their General Practitioner (GP) is considering referral for acupuncture. Sampling will be by consecutive selection, and by randomised allocation to the three branches of the study, in a centralised way following a 1:1:1 distribution (verum acupuncture; sham acupuncture; conventional treatment). Secondly, one patient in three will be randomly selected from each of the acupuncture (verum or sham) groups for a brain perfusion study (by single photon emission tomography). The treatment with verum acupuncture will consist of 8 treatment sessions, once a week, at points selected individually by the acupuncturist. The sham acupuncture group will receive 8 sessions, one per week, with treatment being applied at non-acupuncture points in the dorsal and lumbar regions, using the minimal puncture technique. The control group will be given conventional treatment, as will the other two groups.

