Acupuncture is widely used to treat headache, and can be applied as the sole therapy or as part of a more complex treatment programme [13,14]. Despite its popularity, there persists some controversy as to the differentiation between the specific and the nonspecific effects of acupuncture. A Cochrane review published in 2001 [15] concluded that, in general terms, current evidence supports the value of acupuncture as a treatment for idiopathic headaches, but due to clinical heterogeneity and the low methodological quality of the 26 studies included, it was not possible to make direct recommendations for clinical practice. Fundamentally, some forms of acupuncture seem to be beneficial, but it is unclear as to which treatment strategies (acupuncture points, type of stimulation, frequency, etc.) should be favoured.

The three most recent studies published, during the last two years, report conflicting results. Two studies, which can be classified as belonging to the German strategy of assessing the coverage of acupuncture for certain processes, concluded that both verum acupuncture and sham acupuncture (superficial acupuncture at points not considered to be acupuncture points) are more effective than remaining on the waiting list, untreated [13], but that their results did not differ significantly from those obtained by pharmacological treatment [16]. The third study was a pragmatic one that concluded that acupuncture produces a clinically significant improvement in patients suffering chronic headache, especially in the case of migraine, compared with conventional treatment; moreover, it leads to decreased consumption of medication, visits to the GP and days off work [14]. Endres et al., in a recent review of the subject, concluded that acupuncture treatment for 6 weeks is not inferior to preventive pharmacological treatment for 6 months, but that the use of acupuncture at specific points, needle stimulation and the depth of the puncture are not as important as had previously been thought [17].

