### Randomisation and treatment allocation

Sampling will be by consecutive selection, in accordance with inclusion-exclusion criteria, over a period of 24 months until the predetermined sample size has been obtained. Randomised allocation to the three arms of the trial will be carried out using an appropriate computer program (EpiDat v 3.1), in a centralised way (by the Research Unit at Hospital Costa del Sol, Malaga), following a 1:1:1 distribution (verum acupuncture: minimal acupuncture: conventional treatment), with a sequence for each clinic in blocks of 9. Secondarily, one patient in three will be randomly selected from each of groups A and B to be given a SPECT brain perfusion study. Neither the centres nor the doctors participating in the trial will take part in the randomisation procedure, and the sequence of the latter will remain concealed until the completion of the trial. The patients who fulfil the criteria for inclusion and who give their informed consent will be included in the trial. After each patient's inclusion, his/her GP will contact the randomisation centre, where the patient will be registered, and the doctor will be told, by phone and by fax, which of the three arms of the trial the patient has been allocated to. This procedure guarantees that the randomisation process will not be influenced by the doctor participating. We shall endeavour to ensure that all participants begin the trial with the same expectations of effectiveness; accordingly, the initial information provided to the patient will state that all the treatments provided in the course of the trial are effective [13,14,16].

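### The patient information states without qualification that every trial treatment is effective, which does not fit the protocol's own account of the evidence and cannot be relied on to equalise expectations

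*Protocol article*

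**What the plan says.** Protocol article, Randomisation and treatment allocation: the aim is given as "We shall endeavour to ensure that all participants begin the trial with the same expectations of effectiveness". To that end, "the initial information provided to the patient will state that all the treatments provided in the course of the trial are effective", with references 13, 14 and 16 in support. No qualification is given and no arm is excepted, so sham falls within the statement although it is not named.

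Background, on those same three references: "The three most recent studies published, during the last two years, report conflicting results".

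Abstract, Background, on the effectiveness of acupuncture for migraine: "it remains a controversial issue". The stated aim is to find out whether acupuncture in primary care does better than conventional treatment.

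Abstract, Methods/Design: eligible patients are those "for whom their General Practitioner (GP) is considering referral for acupuncture". Conventional treatment goes to all three groups.

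Design: patients are blinded only between verum and sham. Results measures and Primary outcome measure: migraine days come from the patient's headache diary.

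**The concern.** Two things look wrong.

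The first is consistency. Patients would be told as settled something that the protocol elsewhere treats as unsettled, and the support cited is the very set of studies that the protocol says disagree. Consent would then rest on a firmer statement than the protocol's own reading of the evidence.

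The second is whether the statement does its job. The same words reach three arms that are not alike from the patient's side. Two arms get something new on top of usual care; the third knowingly gets usual care alone. If the statement acts more strongly on a new procedure than on familiar care, expectations after allocation are unequal, and a self-reported count of migraine days is open to that. At stake are the comparisons of each acupuncture arm with conventional treatment, the first of which is the trial's stated aim.

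**Working it through.** The protocol attaches no figure to this point, so the check is a comparison of sections, followed by simple algebra for the contrasts.

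**Step 1: what the cited studies support, on the Background's own summary.**

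| Source | What the protocol reports | Bearing on the claim that all are effective |
|---|---|---|
| Reference 13 | Verum and sham both better than an untreated waiting list | Supports both needled arms against no treatment |
| Reference 16 | No significant difference from drug treatment | Does not separate the options |
| Reference 14 | Acupuncture better than conventional treatment | Favours acupuncture; conflicts with reference 16 on the comparison |
| Background, drug treatment | Effectiveness corroborated, but limited | Some support for conventional care, qualified by the protocol itself |

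Each arm therefore has some support. The conflict lies mainly in how the options compare with each other. An unqualified statement omits both that conflict and the protocol's own word on the limits of conventional treatment.

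**Step 2: does the statement reach the arms equally?**

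- Being considered for acupuncture is an entry condition for everyone, so it does not distinguish the arms at the start.
- After allocation, A and B have conventional care plus a new procedure declared effective.
- C has conventional care only, prescribed by the GP, and knows it.

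**Step 3: effect on the contrasts.** Let e_A, e_B and e_C be the change in reported improvement (in migraine days) that the statement causes in each arm. Then

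- observed A–C difference = true difference + (e_A − e_C)
- observed B–C difference = true difference + (e_B − e_C)
- observed A–B difference = true difference + (e_A − e_B)

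Patients in A and B get the same statement and are blinded to which needling they receive, so e_A = e_B is reasonable and the A–B contrast is unaffected. If e_C equals the other two, A–C and B–C are unaffected as well. Nothing in the design secures that last equality, because C is open and receives no new procedure.

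**Step 4: can the sign and size be fixed?** No. If the statement mainly raises hope in a new procedure, e_A − e_C is positive and favours acupuncture. If it mainly reassures C patients that their care works, e_A − e_C is negative and narrows the difference. The documents give no value for any of the three terms. The planned difference of 1.6 days (Sample size) says what matters to the trial, not how large this effect is.

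**Step 5: could it be detected?** Evaluation of treatment credibility describes ratings in groups A and B only, after the fourth session. That informs the A–B comparison. As described, it does not show whether C held the same expectation.

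**The case against.** The strongest case against is this. The trial's question is comparative, and saying that all options are effective is compatible with not knowing which is best. On the protocol's account each arm has some support. The statement covers all three arms and is expressly meant to equalise expectation, and an equal shift cancels in every contrast. A–C and B–C are open comparisons by design, so hope in the needled arms or disappointment in C would arise under any wording; reassuring C might even narrow the gap. The article gives one clause of paraphrase, the actual information sheet is not shown, and ethics approval is recorded.

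Much of this stands. A reader might infer that patients are told something false; Step 1 does not support that. A reader might infer that the statement tilts the trial towards acupuncture, or that the tilt can be put in days; the documents fix neither direction nor size. A reader might infer that it hampers the verum–sham comparison; both arms get the same message under mutual blinding, and the documents give no ground for supposing a limit on improvement that would compress the difference.

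Two things do not fall. The protocol describes the same three studies as conflicting in one section and cites them for an unqualified claim in another. And cancellation needs equal shifts in all arms, which an open control arm without a new procedure does not secure. Ethics approval does not reconcile the sections.

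**Conclusion.** The point holds in a limited form. The statement is unqualified and inconsistent with the Background and the Abstract; it is not shown to be untrue. It cannot be relied on to give equal expectations across the three arms, so it is a plausible risk to A–C and B–C, of unknown size and uncertain direction. It should not bias A versus B.

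This rests on three assumptions: that the information sheet carries the statement as the article paraphrases it; that it is given before allocation, which is the natural reading of initial information meant to set expectations at the start; and that diary reporting can respond to expectation. The change is worth making because it restores consistency at almost no cost, not because a bias has been measured.

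**What to change.** In Randomisation and treatment allocation, keep the aim of equal expectations but replace the sentence on effectiveness with one neutral text, identical for all patients: it is not known which of the three options works best, and each patient has an equal chance of being allocated to each. This agrees with the Abstract, the Background and the 1:1:1 allocation. Bring the information sheet into line.

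Cost: ethics committee approval of the revised wording and possibly slightly slower enrolment. Design, sample size and analysis are unchanged. The new wording reduces the expectancy gap against the open control arm at best; it does not remove it, so A–C and B–C must still be read as open-label comparisons.

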### Criteria and procedure for withdrawal of patients from the trial

A patient may be withdrawn from the trial at any time, at his/her own discretion or at that of the researcher. The reasons for interrupting the patient's participation in the trial will be recorded on the summary page of the Data Record Book (DRB). If there is any suspicion of secondary headache or of a malignant pathology, as well as the patient being withdrawn from the trial, he/she will be referred to his/her GP so that a conclusive diagnosis may be made on the basis of relevant complementary tests, or so that referral to a neurologist may be considered.

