### Sample size

In calculating the sample size, we assumed a power of 90% and α value of 5%, in order to detect a difference of 1.6 days with migraine with a standard deviation of 2.8 days; this implies a sample size of 72 per group in a design with three equal groups. We propose to recruit 270 patients in order to allow for a 20% withdrawal rate.

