### Results measures

Each patient will fill in a headache diary during the 4 consecutive weeks immediately before the trial (baseline period), and during the 4 weeks following it (see figure 1). The diaries will be complemented with information on 4 additional weeks, from week 21 to week 24 after randomization (the follow-up period) Headache severity should be recorded in the diaries on a 3-point scale, by which 1 represents the presence of mild pain, 2 represents moderate pain and 3, severe pain (with incapacity to carry out everyday activities or necessity to remain in bed). The diary will also record the symptomatic and/or prophylactic medication taken, specifying the brand name and the number of doses. It should be clearly stated on the cover of the diary that the information contained within it is confidential. In addition, before starting the treatment, and also at 12 and 24 weeks after starting it, the patients will be requested to fill in a questionnaire with sociodemographic data and information concerning days off work because of headache; this will be compiled together with the Goldberg Anxiety-Depression Scale register and the results obtained from the Spanish version of the Headache Impact Test [36] and the SF-12 Health Survey (version 2). The purpose of this is to evaluate health-related aspects of the patient's quality of life [37]. The adverse effects of the techniques under study, and those of any rescue medication taken by the patient, will also be recorded. During the baseline evaluation, the patient will be asked to provide an anamnesis of the characteristics of the headache, in accordance with the recommendations of the International Headache Society, in order to classify the type of headache and to assess the term of the pain. Following this, an anamnesis and examination will be performed in accordance with the norms of traditional Chinese medicine.

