#### Primary outcome measure

▪ The difference in the number of days with migraine (DWM) between the baseline period and the period spanning weeks 9–12 (DWM1).

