#### Statistical analysis

Two types of population will be analysed: (1) population per intention to treat (ITT), with all the patients randomised; (2) population per protocol (PP), including only the patients presenting minor differences from the protocol. During analysis, the study groups will be anonymised in order to minimize biased reporting.

The baseline variables among the different groups will be compared to test the homogeneity produced by random allocation, in terms of the differences of means and proportions. The magnitude of the difference in the possible unbalancing produced by the random allocation among the groups will be evaluated using ratios of means and proportions (using that of the sham group as the reference level), and the final fit will be calculated by secondary analyses with multiple linear regression models. In the raw analysis (without fitting), significance tests will be used for the comparisons between *k *samples (parametric or not, depending on whether the distribution of the results variables is asymmetric or otherwise, and on the homogeneity of their variances), taking the control group (group C) as the reference level, and using comparison tests for the differences of the means in the main results variable (DWM1), both for the intergroup comparisons (for independent samples) and for the comparisons between the baseline and the final levels for each group (in the latter case, using tests for non-independent or paired samples).

For the main results variable (DWM1), linear regression models will be constructed, adjusted for the baseline level and analysing per ITT. The group variables will be included, taking the control group as a reference, together with the sociodemographic variables (age and sex) and the baseline variables of the severity of the complaint (pain intensity and frequency). We will adjust for possible confounders using criteria of statistical significance and of confusion. The detection of possible interactions with the treatment group variable will be evaluated by criteria of statistical significance for the corresponding interaction terms. The level of significance will be established at α < 0.05. The model will be reconstructed, removing all the observations with Cook's distances above the 90^th ^percentile of the distribution, in order to test the consistency of the results obtained.

It is our intention to perform an economic analysis from the standpoint of the Andalusia Public Health Service.

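### Withdrawal is from the trial rather than from study treatment only, so patients withdrawn during the 8 treatment weeks have no observed primary outcome for the ITT analysis

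*Protocol article*

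**What the plan says.** All references are to the protocol article.

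- **Criteria and procedure for withdrawal of patients from the trial.** The general rule is "A patient may be withdrawn from the trial at any time, at his/her own discretion or at that of the researcher". No criteria are given for the researcher's discretion. A second trigger follows: "If there is any suspicion of secondary headache or of a malignant pathology, as well as the patient being withdrawn from the trial", with referral to the GP for diagnostic work-up or possible neurology referral. On records, the section says: "The reasons for interrupting the patient's participation in the trial will be recorded on the summary page of the Data Record Book (DRB"). It does not mention diaries or questionnaires after withdrawal.
- **Statistical analysis.** The first analysis set is the "population per intention to treat (ITT), with all the patients randomised". For DWM1, "linear regression models will be constructed, adjusted for the baseline level and analysing per ITT".
- **Primary outcome measure.** DWM1 is the difference in migraine days "between the baseline period and the period spanning weeks 9–12 (DWM1").
- **Results measures.** Diaries are kept for 4 weeks before the trial, "during the 4 weeks following it (see figure 1"), and again in weeks 21–24. Questionnaires are completed before treatment and at 12 and 24 weeks.
- **Design.** The 4 baseline weeks are followed by 8 weeks of treatment and 16 weeks of follow-up.
- **Sample size.** After deriving 72 per group: "We propose to recruit 270 patients in order to allow for a 20% withdrawal rate".

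**The concern.** An intention-to-treat analysis needs outcomes from patients whatever happens to their treatment. The withdrawal section does not distinguish a patient who stops needling from one who leaves follow-up; both are out of the trial. Two of its triggers do not come from the patient: the researcher's discretion, and a suspicion that the later work-up may not confirm.

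The diary schedule makes this costly. With no headache diary during treatment, a patient withdrawn in that period does not have even a partial post-randomisation record of migraine days. At stake is whether the primary comparison uses observed data on everyone randomised, or instead rests on assumptions about those who left. A changed or worsening headache could plausibly prompt suspicion and is related to the outcome, so the missing values need not be a random subset.

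**Working it through.** **1. When DWM1 is observed.** This sets the timeline in Design beside the diary periods in Results measures and the outcome window in Primary outcome measure.

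| Period | Weeks from randomisation | Headache diary scheduled |
|---|---|---|
| Baseline | the 4 weeks before | yes |
| Treatment | 1–8 | none stated |
| Primary outcome window | 9–12 | yes |
| Between windows | 13–20 | none stated |
| Follow-up window | 21–24 | yes |

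The start at week 9 is an inference. Results measures speaks only of the 4 weeks after the trial, and Figure 1 is not shown, but the primary outcome definition fixes weeks 9–12. If participation ends before week 9, the patient has a baseline value and no DWM1. If it ends within weeks 9–12, the record is partial. If it ends after week 12, DWM1 is complete.

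**2. The plan's own figure.** Taking the 72 per group as stated:

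- 72 × 3 = 216
- 216 / (1 − 0.20) = 270, or 90 per group, which reproduces the recruitment target exactly
- 270 − 216 = 54, or 18 per group if evenly spread

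The target therefore treats withdrawn patients as contributing nothing. Because it counts withdrawals for any reason and at any time, 54 is an upper planning figure and not a forecast of missing DWM1.

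**3. Possible bias in a completer comparison.** Let p be the fraction of an arm withdrawn before the outcome. Let d be the amount by which the mean change of withdrawn patients differs from that of completers, after whatever the baseline adjustment removes. The completer mean then misses the all-randomised mean by p × d, and the contrast between arms 1 and 2 is off by p1 × d1 − p2 × d2. With the same d in both arms this is d × (p1 − p2).

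The documents give neither p by arm nor d. Assumed: d = 1.4 to 2.8 days (0.5 to 1 times the plan's SD of 2.8), and withdrawal averaging 20%.

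| Assumed withdrawal | Imbalance | d = 1.4 | d = 2.8 |
|---|---|---|---|
| 20% v 20% | 0 | 0 | 0 |
| 25% v 15% | 0.10 | 0.14 days | 0.28 days |
| 30% v 10% | 0.20 | 0.28 days | 0.56 days |

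Against the 1.6-day target difference, 0.14/1.6 = 9% and 0.56/1.6 = 35%. The top figure needs a threefold imbalance together with a full SD.

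**4. Effect on power.** Two-sided 5% pairwise comparison, normal approximation: power = Φ(1.6 / (2.8 × √(2/n)) − 1.96).

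- n = 72: 1.6/0.467 − 1.96 = 1.47, power 92.9%
- n = 90: 1.6/0.417 − 1.96 = 1.87, power 96.9%

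Keeping every patient would thus gain at most about 4 points. The benefit lies mainly in validity.

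**The case against.** Intention to treat as defined here is a set of patients and does not require complete data. A completed headache diary is an inclusion criterion (Study subjects), so every randomised patient has a baseline value. An all-randomised analysis by imputation with sensitivity analyses is possible, and the rules for it commonly sit in the SAP, which is not shown. **This stands.** A reader might infer that the promised ITT analysis cannot be delivered; the documents do not support that. What remains is that no SAP can recover diaries that were never collected. Whether collection continues is a rule of trial conduct, and the article has a section on it.

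The article nowhere forbids collecting diaries after withdrawal or readmitting a patient whose migraine is confirmed. **This stands in part.** It is silent on both, but ending participation in the trial, with a target that counts withdrawn patients as lost, points towards collection stopping.

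A reader might also infer that patients doing badly would be removed mainly from the two acupuncture groups, by physicians who know the allocation, which would favour acupuncture. **The documents do not support this.** The treating physicians do know the allocation (Data compilation), but the withdrawal section does not say who the researcher is, and an assessor blind to treatment records most of the data. Nowhere is it stated that group C has no scheduled contact; it is under GP care, data are recorded weekly, and disappointed group C patients might leave more often.

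Finally, 54 should not be read as the number who will lack a primary outcome. It includes patients who leave by choice, which is their right and no defect, and patients who leave after week 12. The suspicion rule has an evident rationale too, since secondary headache is an exclusion criterion.

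**Conclusion.** The point holds in a limited form. As written, the withdrawal rule ends participation in the trial, and nothing provides for outcome collection afterwards. For patients withdrawn during the 8 treatment weeks, the ITT analysis of DWM1 cannot rest on observed data: it would depend on imputation or become a completer analysis. The withdrawal and analysis sections need to be reconciled.

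The size is open. Up to 54 of 270 patients are planned as non-contributing, and the share due to researcher decision or suspicion is unknown and may be small. The direction of any bias is also unknown. The range of 0.14 to 0.56 days rests wholly on the assumed imbalances and an equal d in the arms compared. This conclusion also relies on reading the first post-treatment diary as weeks 9–12. It is a cheap improvement to the protocol and does not invalidate the design.

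**What to change.** In the withdrawal section, replace the single category by two:

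- **(a) Study treatment stopped**, for any reason, including researcher decision or suspected secondary headache. The weeks 9–12 and 21–24 diaries and the week-12 and week-24 questionnaires are still collected, and the patient stays in the ITT set.
- **(b) Consent to follow-up withdrawn by the patient.** Only this ends data collection.

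Record the category and date with the reason already required. Handle a later confirmed secondary headache in a sensitivity analysis that omits those patients, keeping them in the main ITT analysis. Leave the clinical referral as written; this change concerns data collection only.

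The cost is a change of protocol wording, with matching consent wording where needed, and the use of existing instruments. The small downside is some effort to obtain diaries from patients who stopped treatment; some will not return them, so a missing-data method is still needed.
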